i.To investigate whether vitamin D supplementation can improve anthropometric status and body composition in nursing women with overweight or obesityii.To investigate whether vitamin D supplements can improve the vitamin D status of these womeniii.To investigate what amount of vitamin D supplementation can reduce the serum level of parathyroid hormone (PTH) in these women

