### Sample size estimation

Sample size was calculated according to Roosta et al. [29] using two mean comparison formula. In this formula, considering α = 0.05, β = 0.2, and mean (standard deviation) of waist circumference changes after supplementation with vitamin D, which was equal to 1.91 cm (1.7) and 0.55 cm (1.04), respectively, in the intervention and control groups, sample size is estimated as 18 subjects. Since, there are three groups in this study, the calculated sample size was multiplied with $$ \sqrt{number\ of\ groups} $$, and finally the desired sample size for this study was obtained as 90 subjects (30 subjects per group).

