### Statistical analysis

Missing data will be imputed using the regression imputation method. Quantitative variables will be reported as mean (standard deviation) and qualitative variables will be reported as percentages. ANOVA and Chi-square tests will be used to compare quantitative and qualitative variables in the three groups. To evaluate the effect of vitamin D supplementation on visceral fat mass, visceral fat percentage, lean mass, body fat percentage, waist circumference, FMI, RFM, BMI, and biochemical factors such as serum 25(OH)D, PTH, calcium and phosphorus levels two-way Repeated Measures ANOVA (RMA) will be applied in SPSS software version 21 (SPSS Inc., Chicago, USA). RMA assesses whether the mean changes in the results from baseline to 12 weeks differ in the three groups. This statistical analysis measures time to group interaction term. There are no planned interim analyses. The 95% confidence level will be considered.

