## Discussion

A large body of growing evidence shows that dairy products, calcium, and vitamin D play a role in regulation of body fat mass [34]. In addition, vitamin D may increase lean body mass [35] and inhibit the development of adipocytes [36]. These effects of vitamin D may be mediated by 1,25-(OH)D3 or through suppression of PTH [35]. However, there are no clinical trials on the effects of vitamin D supplementation on body composition among nursing women with overweight or obesity. Moreover, these kinds of multifactor studies are heterogeneous with regard to doses and types of vitamin D, length of follow-up, outcome ascertainment methods, prevalence of vitamin D deficiency, and other characteristics.

The main purpose of this study is to evaluate the role of vitamin D supplements in body composition among nursing women with overweight or obesity. We hope to provide guidance for the postpartum period, especially for mothers who are at risk of vitamin D deficiency, such as nursing women with overweight or obesity, to improve their vitamin D status by presenting the best dose of vitamin D supplement. This study also will provide more information on the effect of vitamin D on body composition. According to the high prevalence of vitamin D deficiency in pregnant and nursing women, these results may be used to convince governmental organizations providing free vitamin D supplements for these high-risk groups, to improve serum vitamin D levels, in addition to reduce the complications of vitamin D deficiency in nursing women.

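### The three-group interaction test cannot show which dose works, although one objective asks about amount and the trial was sized on an intervention-versus-control contrast

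*Protocol article*

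**What the plan says.** All references are to the protocol article.

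- **Statistical analysis.** One method is named for the treatment effect on all listed body-composition and biochemical outcomes, including 25(OH)D and PTH: a two-way repeated-measures ANOVA read through the time-by-group interaction. Its purpose is stated: "RMA assesses whether the mean changes in the results from baseline to 12 weeks differ in the three groups". The ANOVA and chi-square tests also named there compare all three groups at once. The article gives no dose-versus-placebo or dose-versus-dose contrast, no trend test and no multiplicity rule.
- **Background, objective iii.** "To investigate what amount of vitamin D supplementation can reduce the serum level of parathyroid hormone (PTH) in these women". Objectives i and ii ask only whether supplementation helps.
- **Discussion.** The authors hope to guide mothers on vitamin D status "by presenting the best dose of vitamin D supplement".
- **Sample size estimation.** The size was found "using two mean comparison formula", "considering α = 0.05, β = 0.2", from waist circumference changes, "which was equal to 1.91 cm (1.7) and 0.55 cm (1.04), respectively, in the intervention and control groups".

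**The concern.** The article asks a question about amount, sizes the trial on intervention versus control, and then fixes a test that delivers neither a dose-specific answer nor that contrast. If the section is followed as written, a significant interaction leaves objective iii unanswered. Any statement about a dose would have to come from comparisons chosen after the data are seen. Two unadjusted tests at 0.05 carry a familywise error of about 1 − 0.95² = 9.8%, and three about 1 − 0.95³ = 14.3% (treating them as independent). The Discussion expects the results to be used to persuade government bodies, so the basis of a dose statement matters.

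**Working it through.** **Inputs** (Sample size estimation; the dropout limit is in Strengths and limitations)
- Difference in mean change: 1.91 − 0.55 = 1.36 cm.
- SDs 1.7 and 1.04; root mean square √[(1.7² + 1.04²)/2] = 1.409 cm.
- Alpha 0.05 (two-sided assumed, as the side is not stated); power 0.80.
- 30 per group; with 10% dropout, 27.

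**The plan's own figure.** n = 2 × [1.409 × (1.960 + 0.842)/1.36]² = 16.85, so 17 per group. The t-distribution version gives 18 (power 80.3%), which matches "sample size is estimated as 18 subjects". Next, 17 × √3 = 29.4, which rounds up to 30 per group and 90 in total. The printed 18 would give 18 × √3 = 31.2, so 32. That small discrepancy does not affect this point. The calculation is for one two-group contrast.

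**What the omnibus test can distinguish.** With two visits, the interaction test equals a one-way ANOVA on change, with noncentrality λ = n Σ(μᵢ − μ̄)²/σ². Means are in the order placebo, 2000 IU, 4000 IU.
- Only the 4000 IU arm differs (0.55, 0.55, 1.91): Σ = 0.4533² + 0.4533² + 0.9067² = 1.233.
- Both doses work equally (0.55, 1.91, 1.91): Σ = 0.9067² + 0.4533² + 0.4533² = 1.233.

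In both cases λ = 30 × 1.233/1.986 = 18.63, and power on 2 and 87 df is 97.4% (95.8% at 27 per group). The test responds identically to two opposite answers to the dose question. In a simulation of 20,000 trials per pattern, Bonferroni-adjusted pairwise contrasts on change separated them. The 2000 IU versus placebo contrast was significant in 1.6% and 90% of trials respectively, and 4000 versus 2000 IU in 90% and 1.7%.

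**Power of dose versus placebo.** At 27 per group the SE is 1.409 × √(2/27) = 0.384 and 1.36/0.384 = 3.55. At alpha 0.025 (two contrasts, Bonferroni), noncentral t with 52 df gives 88.8%. At 30 per group it is 92.1%.

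**Power of 4000 versus 2000 IU.** The article gives no expected difference between doses. Assume half the effect, 0.68 cm, tested unadjusted at 0.05:

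| n per group | SD | SE | Power |
|---|---|---|---|
| 27 | 1.7 | 0.463 | 30% |
| 30 | 1.7 | 0.439 | 33% |
| 27 | 1.409 | 0.384 | 41% |
| 30 | 1.409 | 0.364 | 45% |

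The 95% CI half-width runs from 2.00 × 0.364 = 0.73 cm to 2.01 × 0.463 = 0.93 cm, wider than the assumed difference itself. At SD 1.409, 80% power would need 68 per group. Only if the doses differed by about the full 1.36 cm would power be adequate (82% to 96% over the same four rows).

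**The case against.** The strongest reply is that this is a condensed article and that post hoc contrasts and multiplicity rules commonly sit in an SAP that is not shown. That stands as far as it goes: missing post hoc detail alone would not be a finding. Here, however, the section fixes the model, the term tested and its meaning, and that meaning does not match objective iii or the contrast used for sizing. An unseen SAP may add contrasts, but the published text should still agree with itself.

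It is also fair that only objective iii asks about amount, and only for PTH. The Discussion hopes for a best dose rather than promising one, and its stated main purpose, the role of supplements in body composition, is addressed by the interaction. Arm means and SDs will be reported descriptively.

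A reader might infer two stronger faults, which the document does not support.
- **Halved effect.** Between-subject post hoc tests from a repeated-measures ANOVA compare means averaged over both visits, so they would target 0.68 instead of 1.36 cm. The plan states no such test; it names the interaction, which concerns changes.
- **Wrong error rates from pooled variance.** If both vitamin D arms had SD 1.7 and placebo 1.04, ungated pooled-variance contrasts would run at about 8.1% (4000 versus 2000 IU) and 3.5% (dose versus placebo). The plan states no such contrasts either. With those SDs and equal arms, simulation puts the planned omnibus test at about 5.3%, ordinary two-sample t tests on change at about 5.0 to 5.1%, and the pooled 4000 versus 2000 IU contrast, run only after a significant omnibus test, at about 4.2%.

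**Conclusion.** The point holds as a mismatch between question, sample size and analysis. The stated test can show that the three mean changes differ. It cannot say which dose differs from placebo or whether the doses differ from each other. It remains a valid test of any difference among arms, so this should be corrected but does not undermine the trial.

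The equal power under the two patterns follows from the noncentrality and does not depend on the SD used. The power figures rest on the plan's waist-circumference inputs. The article gives none for PTH or 25(OH)D, the outcomes to which its dose statements refer. The dose-versus-dose figures also rest on the assumed 0.68 cm gap and on an SD between 1.41 and 1.7.

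**What to change.** In Statistical analysis:
1. Make the main analysis the week-12 value adjusted for baseline, with two contrasts, 4000 IU versus placebo and 2000 IU versus placebo, under a stated multiplicity rule (such as Dunnett or a fixed sequence), reported with 95% CIs.
2. Keep the three-group interaction as supportive.
3. Report 4000 versus 2000 IU as an estimate with its CI.
4. Optionally, use arm-specific standard errors as a safeguard, given planning SDs of 1.7 and 1.04.

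In Discussion, limit the best-dose wording to what these contrasts can support.

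The cost is wording only: no new data, visits or participants, and about 89% power per dose-versus-placebo contrast at 27 per group. Rewording does not make the trial able to rank the doses, which is why the third comparison should be presented as estimation.

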### Patient safety

Patients will be monitored weekly during the intervention and any occurrence of adverse events will be reported. Moreover, to examine possible hypervitaminosis D, serum concentrations of calcium at the beginning and end of the study will be measured.

## Discussion

A large body of growing evidence shows that dairy products, calcium, and vitamin D play a role in regulation of body fat mass [34]. In addition, vitamin D may increase lean body mass [35] and inhibit the development of adipocytes [36]. These effects of vitamin D may be mediated by 1,25-(OH)D3 or through suppression of PTH [35]. However, there are no clinical trials on the effects of vitamin D supplementation on body composition among nursing women with overweight or obesity. Moreover, these kinds of multifactor studies are heterogeneous with regard to doses and types of vitamin D, length of follow-up, outcome ascertainment methods, prevalence of vitamin D deficiency, and other characteristics.

The main purpose of this study is to evaluate the role of vitamin D supplements in body composition among nursing women with overweight or obesity. We hope to provide guidance for the postpartum period, especially for mothers who are at risk of vitamin D deficiency, such as nursing women with overweight or obesity, to improve their vitamin D status by presenting the best dose of vitamin D supplement. This study also will provide more information on the effect of vitamin D on body composition. According to the high prevalence of vitamin D deficiency in pregnant and nursing women, these results may be used to convince governmental organizations providing free vitamin D supplements for these high-risk groups, to improve serum vitamin D levels, in addition to reduce the complications of vitamin D deficiency in nursing women.

### Strengths and limitations of the study

The strengths of our protocol study include assessing the different doses of vitamin D supplementation to treat vitamin D deficiency in nursing women with BMI of 25 kg/m^2^ and higher.Also, this study is the first study evaluating the effects of different amounts of vitamin D supplementation on anthropometric status and body composition in nursing women with BMI of 25 kg/m^2^ and higher.Body composition measurements are not assessed by gold standard techniques, which can be considered as a limitation of this study.Possible poor cooperation of some patients is another limitation of this study.The calculated sample size is another limitation of this study. Due to financial constraints, the number of subjects is limited to 90. As such, a 10% dropout is considered the maximum.

### Trial status

The date of protocol registration was 04/11/2018, and the registration number is IRCT20140413017254N6. Recruitment will begin on 05/28/2018, and the approximate date when recruitment will be completed is 08/20/2018.

## Data Availability

Not applicable.

## Abbreviations

25(OH)D: 25-Hydroxy-vitamin D
ANOVA: One-way analysis of variance
BFP: Body fat mass percentage
BIA: Body impedance analyses
BMI: Body mass index
ECL: Electrochemiluminescence
ELISA: Enzyme-linked immunosorbent assay
FMI: Fat mass index
IOM: Institute of Medicine
IPAQ: International physical activity questionnaire
PTH: Parathyroid hormone
RFM: Relative fat mass
RMA: Repeated measures ANOVA
